## Abstract

**Introduction:**

Chronic inflammation is the major pathological feature of Atherosclerosis(As). Inflammation may accelerate plaque to develop, which is a key factor resulting in the thinning of the fibrous cap and the vulnerable rupture of plaque. Presently, clinical treatments are still lacking. It is necessary to find a safe and effective treatment for As inflammation. Simiaoyongan Decoction (SMYA) has potential anti-inflammatory and plaque protection effects. This protocol aims to evaluate the efficacy, safety, and mechanism of SMYA for patients with carotid atherosclerotic plaque.

**Methods/design:**

The assessment of SMYA clinical trial is designed as a randomized, double-blind, placebo-controlled study. The sample size is 86 cases in total, with 43 participants in the intervention group and the control group respectively. The intervention group takes SMYA, while the control group takes SMYA placebo. The medication lasts for 14 days every 10 weeks, with a total of 50 weeks. We will use carotid artery high resolution magnetic resonance imaging (HR-MRI) to measure plaque. The plaque minimum fiber cap thickness (PMFCT) is adopted as the primary outcome. The secondary outcomes include plaque fiber cap volume, volume percentage of fiber cap, lipid-rich necrotic core (LRNC) volume, volume percentage of LRNC, internal bleeding volume of plaque, internal bleeding volume percentage of plaque, plaque calcification volume, volume percentage of plaque calcification, lumen stenosis rate, average and a maximum of vessel wall thickness, vessel wall volume, total vessel wall load, carotid atherosclerosis score, hs-CRP, IL-1β and IL-6, the level of lipid profiles and blood glucose, blood pressure, and body weight.

**Discussion:**

We anticipate that patients with As plaque will be improved from SMYA by inhibiting inflammation to enhance plaque stability. This study analyzes plaque by using HR-MRI to evaluate the clinical efficacy and safety of SMYA. Moreover, we conduct transcriptome analysis, proteomic analysis, and metagenomic analysis of blood and stool of participants to study the mechanism of SMYA against As plaque. This is the first prospective TCM trial to observe and treat As plaque by inhibiting inflammatory reaction directly. If successful, the finding will be valuable in the treatment of As plaque and drug development, especially in the “statin era”.

**Trial registration number:**

This trial is registered on Chinese Clinical Trials.gov with number ChiCTR2000039062 on October 15, 2020 (http://www.chictr.org.cn).

## Introduction

Atherosclerosis (As), occurs in the middle and large arteries, chronic inflammation is its major pathological feature, which may give rise to cardiovascular diseases (CVD), such as ischemic heart disease (IHD) and apoplexy [1]. Although there are excellent lipid-lowering treatments, As-related diseases remain the key source of disability and death worldwide [2]. In 2019, the number of CVD patients reached 523 million, and the death toll was about 18.6 million [3]. It is reported that by 2030, the number of CVD deaths will reach 23.6 million [4]. As-related diseases have high morbidity and mortality, medical expenses are expensive, and impose a huge economic burden on society and families [5, 6]. In America, the cost related to IHD was evaluated to rise from $126.2 billion in 2010 to $177.5 billion in 2040, with a 41% increase in cost [7]. About 80% of worldwide CVD deaths happen in low- and middle-income countries, in these countries, the burden of CVD continues to rise because of the transformation of epidemiology [6]. Early detection of As is mostly in peripheral arteries and carotid arteries (CAs) [8]. CAs seem to be the most significant site of As in the clinic, besides coronary arteries. According to statistics, up to 20% of ischemic stroke patients were caused by carotid As [9]. In 2020, the global carotid plaque patients were evaluated to be 21.1% in the population aged 30–79, equivalent to 816 million affected people [10]. In the global trend of the aging population growing background, more people will be affected by carotid As in the future.

Chronic non-resolving inflammation is an important feature of As [11]. Conventional therapy focuses on lowering blood fat, although plenty of patients have reached goal blood fat levels, they still suffer recurrent clinical events. Under inflammatory conditions, lipid accumulation, and immune cells continuous recruitment triggers the death of lesional cells, resulting in the expansion of the lipid-rich necrotic core (LRNC). Plaque necrosis, accompanied by thinning and fragile fibrous cap, may lead to plaque rupture resulting in acute luminal thrombosis, which will occur in clinical acute events, such as myocardial infarction (MI) or stroke [12]. As a result of the coexistence of inflammatory plaque and coronary artery system, the risk of repeated CVD in patients after MI is 10–12% within one year and 18–20% at three years [13]. The increased residual risk of cardiovascular events is mainly due to inflammation, anti-inflammatory treatment has become a major study direction in the prevention and treatment of As. Therefore, new anti-atherosclerotic therapies, particularly those that can better control inflammation reactions, are needed. At present, As anti-inflammatory medicine is on the rise, such as targeted therapeutic agents which are targeting inflammatory factors, Canakinumab and Tocilizumab, and classic anti-inflammatory medicines, colchicine, and methotrexate. LoDoCo2 and COLCOT trials have proved that anti-inflammatory treatment indeed improves As [14–16]. Yet these potential agents are emphasized may cause a raise in cancer risk and damage to the defense system, and have side effects such as reducing immunity and increasing the risk of infection [11]. Safe and effective treatment for As inflammation is lacking all along.

In recent years, Traditional Chinese Medicine (TCM) has had a wide-ranging impact and is recognized in many regions and countries [17]. Simiaoyongan Decoction (SMYA) is a traditional Chinese formula for treating vascular inflammation. SMYA consists of four traditional Chinese herbs, the composition shown in Table 1, has the effect of clearing heat, detoxifying, invigorating the circulation of blood, and unblocking circulation tracts. SMYA has a significant effect on various diseases, which are based on As lesions, for instance, coronary atherosclerotic heart disease [18, 19]. *Lonicera japonica* Thunb has effects on antibacterial, antiviral, anti-inflammatory, antioxidant, and others, and also has certain effects on the immune system and cardiovascular systems [20]. Chemical composition studies showed that SMYA contained organic acids, flavonoids, iridoids, phenylpropanoids, volatile oil, triterpenoid saponins, polysaccharides, and so on [21–24]. Some experimental research has proved that SMYA may significantly reduce the level of cardiovascular inflammation index hs-CRP and the content of its upstream inflammatory factors, IL-6, IL-1β and so on, the effect mechanism probably related to TLR4, NF-κB, Dll4 or other relevant signal transduction pathways [25–27]. In As rabbit experiment, it was found that the level of some inflammatory cytokines in blood and plaque decreased after taking SMYA, meanwhile, the content of LDL-C and TG also reduced, the thickness of fiber cap and the content of smooth muscle cells (SMCs) might increase, and these improvements contributed to stabilizing vulnerable plaque (VP) [28]. Our team’s clinical research indicated that taking SMYA continuously for 2 weeks might decrease the average serum hs-CRP of patients with carotid atherosclerotic plaque by 57.65%, its curative effect was fast, the repeatability was strong, and the safety was good [29]. 

**Table 1 Tab1:** Composition of Simiaoyongan Decoction

Ingredients	Latinname	Family	Content
Jinyinhua	*Lonicera japonica Thunb*	*Caprifoliaceae*	90 g
Xuanshen	*Scrophularia ningpoensis Hemsl*	*Scrophulariaceae*	90 g
Danggui	*Angelica sinensis (Oliv.) Diels*	*Apiaceae*	60 g
Shenggancao	*Glycyrrhiza uralensis Fisch*	*Fabaceae*	30 g

Yet, the previous atherosclerosis-related TCM research mainly focused on experiments and mechanism exploration, clinical studies were few. Meantime, in terms of efficacy indicators, most clinical studies were limited to assessing the effect of TCM on inflammatory factors and blood lipids in serum or using primary or subjective means such as ultrasound to evaluate As plaque. High-quality randomized, double-blind, and controlled studies on the treatment of As in TCM are lacking.

Numerous magnetic resonance imaging (MRI) studies have identified characteristics of carotid plaque related to cerebral vascular diseases [30], but there is no clinical research associated with TCM. Thus, we design this randomized, double-blind, parallel-controlled study and high resolution magnetic resonance imaging (HR-MRI) is used to correctly assess the efficacy of SMYA in the treatment of carotid atherosclerotic plaque. In the meantime, this study will also explore the internal mechanism of SMYA in the treatment of As, through transcriptome analysis, proteomic analysis, and metagenomic analysis of blood and stool. If successful, the finding will be valuable in the treatment of As plaque and drug development, and provide a reliable evidence chain.

## Methods

### Study design

The assessment of SMYA clinical trial is designed as a randomized, double-blind, placebo-controlled study. The sample size is 86 cases in total, with 43 participants in the intervention group and the control group respectively. The protocol version number is V2.0, version date is September 29th, 2020. The study has also been registered at http://www.chictr.org.cn(ChiCTR2000039062, October 15, 2020). This trial has the following objectives: (1) To evaluate the efficacy of SMYA for carotid atherosclerotic plaque by HR-MRI. (2) To estimate the safety of SMYA. The vital signs, adverse events (AEs), routine blood tests, liver function tests, and kidney function tests are the main indicators to evaluate safety. (3) To research the internal mechanism of SMYA for carotid atherosclerotic plaque by blood transcriptome analysis, blood proteomic analysis, and stool metagenomic analysis. The protocol will be described according to SPIRIT-TCM Extension 2018 (Additional file 1) [31]. 

### Recruitment

The study will be conducted in Dongzhimen Hospital Affiliated to Beijing University of Chinese Medicine (DHABUCM) (Beijing, China). We will release recruitment information through posters, email push, social media publicity, and outpatient service. Patients are involved in the conduct of our research. All subjects must sign an informed consent form before enrollment. Figure 1 shows the flow chart of the trial. At the time of manuscript submission, patient recruitment for the trial is ongoing. The expected recruitment rate is 2 patients per week. The first patient was included on October 20, 2022, and the study is expected to be completed in December 2025.

**Fig. 1 Fig1:**
[figure not shown]
Participant flowchart

### Participants selection

#### Diagnostic criteria

The observed vascular segments are bilateral common CA and internal CA. Color Doppler ultrasound indicates that the local bulge in the target vascular segment is > 0.5 mm from the arterial lumen or exceeds 50% of the surrounding intima-media thickness (IMT) value, or IMT > 1.5 mm, diagnoses carotid atherosclerotic plaque [32, 33].

#### Inclusion criteria

Participants with carotid atherosclerotic plaque under the diagnosis of Color Doppler ultrasound.hs-CRP ≥ 2 mg/L.Participants aged 40–80 years, male or female.Participants can stick to taking medicine for a long time.Signing informed consent voluntarily.

#### Exclusion criteria

Participants with acute or subacute bleeding in plaque.Participants with complete calcification and fibrosis of plaque.Participants contraindicated by MRI, such as carrying cardiac pacemaker, artificial tooth, cardiac stent, and so on.Participants with active ulcers and bleeding tendency.Participants take anticoagulant medicine (such as warfarin) for a long time or are taking dual antiplatelet medicine.Participants with severe arrhythmia, atrial fibrillation, and heart failure, and other severe diseases including the liver, kidney, hematopoietic system, endocrine system, and respiratory system.Alanine aminotransferase (ALT) and/or aspartate aminotransferase (AST) ≥ 1.5 times the upper limit of normal, and/or creatinine (Cr) higher than normal.Participants with any other life-threatening or serious diseases and are unable to complete 50 weeks of treatment.Pregnant or lactating women, and women who have recent pregnancy plans.Allergic to components of the product.Participants with other diseases or mental disorders, who are deemed may limit efficacy evaluation or patient follow-up by the researcher.Participants who have entered into clinical trials of other medicines within 4 weeks.

#### Drop-Out criter

Participants cannot tolerate treatment medicines or control medicines during the trial.Participants with some serious complications, concomitant diseases, or special physiological changes occurring during the trial, and are not suitable to continue the study.During the trial, participants who have poor compliance, used medicines less than 80% of the requisite amount or more than 120% of the requisite amount.Participants added medicines prohibited under this protocol.

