### Randomization, allocation and blinding

The stratified blocked randomization method will be used in this protocol. A random code list will be generated by SAS (6.12), and The intervention group and the control group will be randomly assigned to the enrolled participants in a ratio of 1:1. This study selects double-blind method, subjects, clinical researchers, drug managers, statisticians, and other staff members will be blinded. The trial is also designed as a two-stage blind. The blinding is conducted by irrelevant personnel, and the blind record is formed. In order to ensure the quality of the blind method, all medicaments, including placebo, are required to be packaged uniformly. According to the *Standard for the Use of Food Additives in the National Standard for Food Safety* [34], the placebo is made from 5% raw materials and 95% dextrin based on the type and volume of the raw materials. Adding an extremely low dose of the raw material makes this placebo similar in appearance, color, smell, and taste to the therapeutic drugs, but without any pharmacological effects [35, 36].

The blind bottom will be sealed and stored. If the blind bottom is opened, it is necessary to indicate the person who opened it, the date, the reason, etc., and at the same time record it in the case report form (CRF). In case of emergency, or when the patient needs to be rescued and necessary to know what medicines the patient is taking, The corresponding emergency letters must be opened and read in the presence of researchers and research leaders. Once the emergency letter is opened, the participant with this number will withdraw from the trial, at the same time, CRF will record all details. All emergency letters shall be taken back with the CRFs after the study for blind review.

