#### Guidelines for drug combination

During the trial, original lipid-lowering medicines are allowed to be used, but Western and Chinese medicines that may lower serum hs-CRP or other inflammatory factors are not allowed, for example, antibiotics, Canakinumab, and colchicine. If the participants have concomitant diseases, which they must continue to maintain these medicines or treatments, the diseases, treatment, dosage, usage and use time shall be recorded in the CRF, in order to analyze and report when summarizing. At each visit, the researcher detailed records of whether participants took medicine on time, and recovered the participants’ remaining medicines to judge treatment compliance. Patient compliance = Actual total medication/Total medication required by the protocol×100%.

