#### Outcome evaluation

##### Primary outcome

PMFCT should be recorded at baseline (visit 1) and after treatment (visit 10), and evaluated at the study endpoint.

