### Statistical analysis plan

This study will adopt an intention-to-treat analysis. And statistical analysis will be conducted by special statisticians in a blind way. SAS (6.12) will be used for statistical analysis, all statistical tests are conducted by two-sided tests, and *p* ≤ 0.05 is regarded as statistically significant. We will first analyze the baseline balance to explain whether the intervention group and control group of basic conditions are comparable. Quantitative metrics will be described with a number of cases, mean, standard deviation, median, minimum, and maximum, and t test or Wilcoxon rank sum test will be adopted to compare two groups. Qualitative metrics will be listed in frequency and percentages, and chi-square test or Fisher’s exact test will be conducted to compare two groups. For the analysis of combined medication, we will list the number and percentage, and analyze the differences between the two groups by the chi-square test or Fisher’s exact test. Analysis of treatment compliance will list the number and percentage of cases with experimental drugs < 80%, > 120%, 80-120%, and chi-square test or Fisher’s exact test will be conducted. In terms of safety analysis, we will describe the incidence of AEs and SAEs during the treatment period, and list the detailed tables of AEs and SAEs.

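### The drop-out and emergency-unblinding rules do not separate stopping study drug from leaving follow-up, so they conflict with intention-to-treat unless those participants are still scanned at week 50 and analysed as randomised

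*Protocol article*

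**What the plan says.** **Drop-out criteria (Participants selection).** Four kinds of event after randomisation make a participant a drop-out:
- intolerance: "Participants cannot tolerate treatment medicines or control medicines during the trial";
- complications or other changes that make the participant unsuitable to continue;
- compliance outside a band: "participants who have poor compliance, used medicines less than 80% of the requisite amount or more than 120% of the requisite amount";
- added medication: "Participants added medicines prohibited under this protocol".

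The section Guidelines for drug combination defines the last of these: "Western and Chinese medicines that may lower serum hs-CRP or other inflammatory factors are not allowed, for example, antibiotics, Canakinumab, and colchicine".

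**Randomization, allocation and blinding.** "Once the emergency letter is opened, the participant with this number will withdraw from the trial". The wording concerns the trial, not only the study drug.

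**Primary outcome.** "PMFCT should be recorded at baseline (visit 1) and after treatment (visit 10), and evaluated at the study endpoint". Table 2 shows no HR-MRI between those two visits; visit 10 is at week 50.

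**Statistical analysis plan (section of the article).** "This study will adopt an intention-to-treat analysis". The same section describes compliance by arm: "Analysis of treatment compliance will list the number and percentage of cases with experimental drugs < 80%, > 120%, 80-120" per cent. It names no per-protocol set.

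**Sample size calculation.** 36 per group is raised to 43 to allow for drop-out. The rate is not given.

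**The concern.** Intention-to-treat needs two things: everyone randomised is analysed in the assigned arm, and the outcome is sought from everyone. The second depends on follow-up, which the protocol governs. Here the protocol speaks of dropping out and of withdrawal from the trial, and does not say whether this means stopping study drug or also ending follow-up.

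The difference matters more than usual because PMFCT has a single post-baseline measurement. With no intermediate scan to fall back on, a participant who leaves at week 20 contributes nothing to the primary comparison unless recalled. An analysis plan can define analysis sets, but it cannot recover a scan that was never taken. Recruitment was under way when the article was submitted, so any scan lost under the current wording is lost for good.

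The triggers are also not neutral. Intolerance, infection treated with a prohibited drug, added anti-inflammatory medication and poor compliance may all depend on arm and on prognosis: the placebo is described as pharmacologically inert, while the active product is hypothesised to be anti-inflammatory. Losing these people selectively would undo the randomised comparison while the result still carried the intention-to-treat label.

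**Working it through.** **1. The rules side by side**

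| Event | Stated consequence | Week-50 scan still sought? | Analysed in assigned arm? |
|---|---|---|---|
| Intolerance; unsuitable to continue | Drop-out | Not stated | Covered only by the general intention-to-treat sentence |
| Compliance <80% or >120% | Drop-out | Not stated, but may be known only at visit 10, when the scan is due | As above; also counted in the compliance table |
| Prohibited medicine added | Drop-out | Not stated | As above |
| Emergency code opened | Withdraws from the trial | Not stated; the literal wording points to no | As above |

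The conflict lies in the third column. Intention-to-treat needs the scan to be sought in every row, and no row says that it is.

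**2. The plan's own allowance**

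Inputs (Sample size calculation): 36 needed and 43 recruited per group.
- Implied loss: 1 − 36/43 = 7/43 = 16.3%.
- Check: 36/(1 − 0.16) = 42.9, rounded up to 43. The step from 36 to 43 is reproduced with a drop-out rate of about 16%.

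The 36 itself does not reproduce from the stated inputs (26 per group by the normal formula, 28 by the t-test, at two-sided α = 0.01 and 90% power). That is a separate matter and does not affect this point.

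**3. Is power the issue?**

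Inputs: difference 40 (printed with both a percent sign and a micrometre unit; read here as 40 µm, an assumption), SDs 38 and 36, two-sided α = 0.01. Common SD = √((38² + 36²)/2) = 37.0.

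| Analysed per group | Power (exact t) |
|---|---|
| 43 | 0.99 |
| 36 | 0.97 |
| 30 | 0.93 |
| 28 | 0.91 |

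On the plan's inputs, losing the whole allowance leaves ample power. The issue is bias.

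**4. Size of the possible bias**

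If a share f of one arm is lost, and those lost would have had a PMFCT change worse by k SDs than those retained, the retained mean differs from the all-randomised mean by

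bias = f × k × SD.

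Assumptions: loss in one arm only; k between 0.5 and 1; SD = 37. Only the allowance of 7 of 43 comes from the document.

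| Lost from one arm | k = 0.5 | k = 1 |
|---|---|---|
| 2 of 43 | 0.0465 × 18.5 = 0.9 µm | 0.0465 × 37 = 1.7 µm |
| 7 of 43 | 0.163 × 18.5 = 3.0 µm | 0.163 × 37 = 6.0 µm |

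As a share of 40 µm, the second row is 3.0/40 = 7.5% to 6.0/40 = 15%.

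**5. Effect on the type I error with no true effect**

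With 36 against 43 analysed, SE = √(38²/36 + 36²/43) = 8.38 µm. The test at two-sided 0.05 (the level in the statistical section) is shifted by bias/SE:
- 3.0/8.38 = 0.36, giving an error rate of about 0.065;
- 6.0/8.38 = 0.72, giving about 0.11.

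With 2 lost, the rate is about 0.051 to 0.055. If losses are equal in number and kind in the two arms, or unrelated to outcome, the bias is zero.

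**The case against.** A reader might infer that intention-to-treat cannot be carried out and that the PMFCT analysis will be a selected completer comparison. The document does not support that, for four reasons:

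- **Nothing bars the scan or the analysis.** The drop-out list does not say that drop-outs are refused the week-50 HR-MRI or removed from analysis. People who stop attending are treated under a separate heading on voluntary withdrawal, so a drop-out need not be lost to follow-up. This stands, and it is why the point is conditional.
- **Compliance may be known only at the end.** It is computed over total medication, and the last collection of unused drug is at visit 10, when the scan is due. A non-complier found then can still be scanned; only an analysis rule could exclude that person, and none is stated. This stands for that group. It does not help those who drop out earlier for intolerance, complications, added medicines or a code break.
- **The compliance table is not a contradiction.** Drop-outs can be counted in it, and it suggests that some non-compliers stay in the reported data. This stands.
- **Prohibited medicines are not purely exclusionary.** Read literally, one antibiotic course meets a drop-out criterion. The same section, however, has medicines that must be continued for concomitant disease recorded for analysis. How the two fit together is unclear, so the number of participants affected cannot be inferred.

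It can also be said that analysis sets and missing-data rules belong in a full protocol or analysis plan not shown. That is fair, and their absence is not the complaint. The complaint is that the stated retention rules, followed literally, work against the stated analysis.

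**Conclusion.** The point holds in conditional form. The drop-out criteria and the unblinding rule act after randomisation and leave open whether follow-up ends with study drug. With PMFCT measured only at baseline and week 50, they conflict with the stated intention-to-treat analysis unless dropped and unblinded participants are still scanned and analysed as randomised, which the article does not state.

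If they are not scanned and analysed, the risk is selection bias in the primary comparison. The 3 to 6 µm shift is an illustration, not an estimate: it rests on informative loss of 7 of 43 from one arm only, an assumed deficit of 0.5 to 1 SD, and reading the planned effect as 40 µm. It would favour the arm that loses its worse participants. The document gives no evidence on how many will meet a criterion or whether the arms will differ.

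**What to change.** Reconcile the sections on drop-out, unblinding, concomitant medication and statistical analysis by a short amendment that:

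1. separates stopping study drug from leaving follow-up, in the drop-out list and in the emergency-unblinding paragraph;
2. states that everyone randomised stays in follow-up and is asked to have the week-50 HR-MRI and the other visit-10 assessments, whatever their compliance, added medicines or code break, unless they withdraw consent;
3. states that all of them are analysed in the arm assigned;
4. uses the 80–120% compliance band and the prohibited-medicine rule only to define a supportive per-protocol set.

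Rules on who stops study drug are unchanged. Table 2 already schedules the week-50 scan for every participant, so no new assessment is added. The cost is the amendment, matching wording in the analysis plan, and the effort of bringing back participants who are off drug. As recruitment was ongoing at submission, an early change preserves more scans.
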